## Method

A specifically tailored CBT-based anxiety intervention for South African children with visual impairments will be evaluated in two special schools that cater for children with visual impairments. This study is set up as a randomised wait-list control group design with pre-, post-and follow-up intervention measures, with 60 participants randomly assigned to an IIG (*n* = 30) and a DIG (*n* = 30). Before implementation of the programme 10 participants from each group will be randomly selected to take part in a focus group. The focus group will be aimed at obtaining the participants’ personal inputs and to pilot certain sections of the programme before final implementation. Both of the programme's groups will receive the 10 session anxiety intervention programme**.** The participants will complete baseline (T1), post intervention (T2 for IIG and T3 for DIG) and 3 month (T3 for IIG and T4 for DIG) or 6 month (T4 only for IIG) follow-up assessments.

The research design can be represented as follows:

R  IIG T1   X  IIG T2     IIG T3  IIG T4

R  DIG T1     DIG T2  X  DIG T3   DIG T4

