## Programme evaluation

As mentioned above, all assenting children from School 1 and School 2 will randomly be assigned to 1 of 2 groups at their respective school (an IIG or a DIG). The IIG groups from School 1 and School 2 will be combined to form one large IIG, whilst the DIG groups from School 1 and School 2 will be combined to form one large DIG.

The evaluation phase will comprise both a quantitative and qualitative component (more information about the qualitative component is given below). For the quantitative evaluation, all assenting children in the IIG and DIG (approximately 60 participants) will be administered a short biographical questionnaire (only at T1) and three self-report questionnaires at pre (T1), post (T2), and follow-up (T3 and T4) intervention. Children in the IIG will receive the intervention programme before the children in the DIG. It is envisaged that the programme will be delivered to the two groups (the IIG and DIG) of children according to the following outline:

Initial assessment of all children, IIG and DIG (T1)Children in the IIG receive the anxiety intervention programme (5 weeks)Re-assessment of all children, IIG and DIG (T2)Children in the DIG receive the anxiety intervention programme (5 weeks)Re-assessment of all children, IIG and DIG (T3)Final assessment of all children, IIG and DIG (T4 – It will be 6 months after the children in the IIG received the intervention and 3 months after the children in the DIG received the intervention). Resulting from time constraints, where all assessments should be conducted within one academic year, there will be no 6 month follow-up for the DIG, and no wait period for the IIG.

It will be possible to measure:

The stability of the measures when untreated over time (The DIG will act as a wait-list control group using T1 and T2 comparisons)The impact of the anxiety intervention programme immediately after completion (using immediate pre and post-data from both groups – IIG [T1 and T2]; and DIG [T2 and T3])The maintenance of the effects of the anxiety intervention programme over time following intervention (IIG using T2, T3 [3 month] and T4 [6 month] comparisons, and DIG using T3 and T4 [3 month] comparisons)

The following six hypotheses are to be tested during the evaluation phase of the proposed study (four hypotheses pertain to between group effects and two hypotheses pertain to within group effects).

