### Between group effects

Firstly, it is hypothesised that there will be no significant differences between the scores obtained by the IIG and DIG on the RCADS at T1.Secondly, anxiety scores obtained by the IIG on the RCADS (post intervention) will be significantly lower than the anxiety scores obtained by the DIG on the RCADS at T2.Thirdly, there will be no significant differences in the anxiety scores of the IIG at T2 and DIG on the RCADS at T3.Fourthly, results obtained on the RCADS at post-intervention (T3) will be retained at the three (DIG) and six month (IIG) follow-ups (T4).

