### Teacher outcomes

An additional outcome relates to emotional and behavioural difficulties experienced by group participants. The Strengths and Difficulties Questionnaire (SDQ) is a widely used, brief behavioural screening questionnaire aimed at detecting behavioural and emotional difficulties in youth (aged 3–16 years) (Mostert 2007). The SDQ consists of 25 items which can be divided into five sub-scales of five items each. Four sub-scales comprise the most important domains of child psychopathology, including:

emotional symptomsconduct problemshyperactivity and inattentionpeer relationship problems.

Scores on these sub-scales add up to a total difficulties score. The remaining subscale (pro-social behaviour) measures the child's strengths in social interactions (Goodman 1997). Items are scored on a three-point Likert scale (Goodman *et al.*
2003). Class teachers will be asked to complete the informant version of the SDQ (Mostert 2007) on two occasions for each participant, before and directly after implementation of the anxiety intervention programme. The informant version of the SDQ assesses the teacher's perception of whether a child has a problem or not. Focus is given to chronicity, distress, social impairment and burden. The SDQ has been found to have favourable psychometric properties and the questionnaire was deemed to have good construct validity, as it was found to have substantial correlations with other indices of psychopathology (Goodman, Meltzer & Bailey 1998; Goodman, Renfrew & Mullick 2000; Goodman *et al.*
2003).

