### Statistical analyses

The Statistical Package for the Social Sciences (SPSS) (Van Leeuwen *et al.*
2006) will be used to calculate descriptive and non-parametric statistics. As a result of the envisaged small sample size (*N* = 60), a Mann-Whitney test will be used to determine the significance of differences between the quantitative pre-and-post intervention measures (George & Mallery 2006). Pre-intervention (T1) scores will be analysed to determine the equivalence of the IIG and the DIG, before the intervention and change scores (difference between the pre-and post-intervention scores) for the IIG and DIG will be compared to evaluate change as a result of the intervention programme. Qualitative data will be analysed by means of thematic content analyses.

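### The between-group effect test does not say which assessment is post-intervention, and the protocol's conflicting labels allow it to compare two treated periods

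*Protocol article*

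**What the plan says.** The Method section describes "with 60 participants randomly assigned to an IIG (*n* = 30) and a DIG (*n* = 30"). All children complete the self-report questionnaires at T1, T2, T3 and T4. The immediate group (IIG) has the programme between T1 and T2, and the delayed group (DIG) has it between T2 and T3.

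Statistical analyses gives one test: "a Mann-Whitney test will be used to determine the significance of differences between the quantitative pre-and-post intervention measures". On baseline it says "Pre-intervention (T1) scores will be analysed to determine the equivalence of the IIG and the DIG". On effect it says "change scores (difference between the pre-and post-intervention scores) for the IIG and DIG will be compared to evaluate change" brought about by the programme. The second time point of the change score is not named.

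Other sections use the label post-intervention in different ways:

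- Method is group-specific: "post intervention (T2 for IIG and T3 for DIG").
- Programme evaluation, describing the questionnaires, uses calendar labels for all children: pre is T1, post is T2, and follow-up is T3 and T4.
- Programme evaluation, listing what can be measured, takes immediate programme impact from "IIG [T1 and T2]; and DIG [T2 and T3"]. It assigns the DIG's T1–T2 data to a separate item on stability without treatment.
- Between group effects, fourth hypothesis, calls T3 post-intervention for both groups.

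The second hypothesis states that IIG scores after the programme "will be significantly lower than the anxiety scores obtained by the DIG on the RCADS at T2". Under Teacher outcomes, class teachers complete the SDQ "on two occasions for each participant, before and directly after implementation of the anxiety intervention programme".

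**The concern.** T1 to T2 is the only interval in which one randomised group is treated and the other is not. A between-group test of change measures the programme's effect only if both change scores cover that interval. If the DIG's score ends at T3, it too contains the programme, and an effective programme is expected to show no difference between the groups.

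The word that decides this is left open in the only effect test described. The list item that comes closest to the test's stated purpose, immediate programme impact, pairs IIG T1–T2 with DIG T2–T3. An analyst who takes the time points from that item would build an uninformative comparison. An open definition also leaves room to choose the contrast after the data are seen.

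The SDQ matters separately. The RCADS is collected from everyone at all four times, so the right contrast can always be recovered. The SDQ is collected only twice per child, so a poor choice of occasions cannot be repaired at analysis.

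**Working it through.** The article states no power, alpha or effect size, so there is no planned figure to reproduce. The check is what each reading of the post label does to the test.

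**Expected contrast.** Let the programme lower the mean score by d, with the same effect in both groups, retained to T3, and no time trend. Means at T1, T2 and T3 relative to baseline are then 0, −d, −d in the IIG and 0, 0, −d in the DIG.

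| Reading | IIG change | DIG change | Expected difference |
|---|---|---|---|
| T1–T2 in both (calendar labels) | −d | 0 | −d |
| IIG T1–T2, DIG T2–T3 (programme-impact item) | −d | −d − 0 = −d | 0 |
| IIG T1–T2, DIG T1–T3 (pre = T1, Method's post) | −d | −d | 0 |
| T1–T3 in both (fourth hypothesis's post) | −d | −d | 0 |

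Only the first reading carries information on efficacy. Labelling pre-intervention as T1, as Statistical analyses does, rules out the second row if applied strictly. It does not rule out the third or fourth, because the post label decides whether the DIG has been treated.

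**Inputs for the size.**

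- From the document: 30 per group and the Mann-Whitney test.
- Guided by the document: correlation r between occasions. Participant outcomes gives one-week test-retest values of .65 to .80 for the RCADS scales; .5 to .8 was used because the intervals here are longer.
- Assumed: two-sided alpha 0.05, normal scores with SD 1, and d = 0.3, 0.5 or 0.8.

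The SD of a change score is √(2(1 − r)): 1.00 at r = .5, 0.84 at .65 and 0.63 at .8.

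**Simulated rejection rates** (4,000 runs per scenario):

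| d | r | T1–T2 in both | IIG T1–T2 vs DIG T2–T3 |
|---|---|---|---|
| 0.3 | .5 | 0.197 | 0.055 |
| 0.3 | .65 | 0.255 | 0.053 |
| 0.3 | .8 | 0.409 | 0.050 |
| 0.5 | .5 | 0.447 | 0.049 |
| 0.5 | .65 | 0.597 | 0.045 |
| 0.5 | .8 | 0.831 | 0.047 |
| 0.8 | .5 | 0.840 | 0.046 |
| 0.8 | .65 | 0.943 | 0.051 |
| 0.8 | .8 | 0.998 | 0.045 |

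The last column stays at the type I error rate for every effect size. Simulating the third and fourth readings at 0.6 and 1.0 SD likewise gave about 4–5%.

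**SDQ.** If the two ratings are timed by each child's own programme, they fall at T1 and T2 in the IIG and at T2 and T3 in the DIG. The change scores are those of the second reading, and no DIG child has a rating at T1. What survives is an unadjusted comparison at T2, where the IIG has its second rating and the DIG its first.

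**The case against.** A reader might infer that the plan defines its effect test as treated against treated and so cannot detect an effect. The document does not support that. Statistical analyses labels pre-intervention as T1 for both groups. Programme evaluation gives calendar labels for all children and says that the DIG serves as wait-list control over T1 and T2. The second hypothesis compares the groups at T2, and the Discussion expects lower symptoms in the IIG than in the DIG. The third hypothesis sets IIG at T2 against DIG at T3 and expects no difference, so the authors did not regard that kind of comparison as the efficacy test. The item pairing IIG T1–T2 with DIG T2–T3 matches the two within-group hypotheses and does not say that the two changes are compared with each other. All of this stands, and it makes T1–T2 in both groups the likely intent.

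Nor is the second hypothesis a further incompatible version of the test. Under randomisation, T2 scores and T1–T2 change both estimate −d over the same period. They differ in precision, not in target.

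It can also be said that an exact change-score window may be left to an analysis plan that is not shown. Silence alone would be no finding. Here, though, the article itself gives the key word several meanings, and a reader cannot tell which one governs the test.

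On the SDQ, Teacher outcomes gives no T-labels, so own-programme timing is an inference, though the natural one for wording that applies to each participant. The SDQ is an additional outcome that none of the six hypotheses uses. To say that it would have no control at all goes too far, since the T2 comparison remains.

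**Conclusion.** The point holds as an inconsistency in the definition of the key contrast. It does not show that the plan as a whole is unable to find an effect. The post-intervention time point is not fixed in the effect test and has conflicting meanings elsewhere. T1–T2 in both groups is the better supported reading. The group-specific labels nevertheless permit comparisons with an expected difference of zero.

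The stakes are about 5% rejection under those readings, against roughly 0.20–0.41, 0.45–0.83 and 0.84–1.00 at 0.3, 0.5 and 0.8 SD under T1–T2. The 5% figure rests on equal, retained effects and no time trend. If these fail, the treated-versus-treated test may reject more often, but for reasons that do not measure efficacy. Alpha, effect sizes and the exact correlations are assumptions.

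For the teacher SDQ, the natural reading leaves the DIG without an untreated change score, and later analysis cannot supply one.

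**What to change.** - **Statistical analyses:** state that the effectiveness test compares T1-to-T2 change in the IIG with T1-to-T2 change in the DIG.
- **Programme evaluation:** label DIG T2–T3 change as an uncontrolled within-group replication, separate from the randomised contrast.
- **Method, Programme evaluation and Between group effects:** use one meaning for post-intervention, or replace it with the T-label throughout, including in the fourth hypothesis.
- **Teacher outcomes:** specify that teachers rate all children at T1 and T2.

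For the RCADS the cost is wording only, since it is already collected from everyone at both times. For the SDQ the number of forms stays at two per child. The DIG then has no post-programme teacher rating. If that is wanted, a third rating at T3 adds one form per DIG child, about 30 in all.

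### The one named between-group efficacy test uses change to post-intervention, a time point the protocol defines in conflicting ways; one of these would set treated children against treated children

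*Protocol article*

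**What the plan says.** Statistical analyses names one inferential test: "a Mann-Whitney test will be used to determine the significance of differences between the quantitative pre-and-post intervention measures". It describes two uses. The first is a baseline check: "Pre-intervention (T1) scores will be analysed to determine the equivalence of the IIG and the DIG". The second is the efficacy comparison: "change scores (difference between the pre-and post-intervention scores) for the IIG and DIG will be compared to evaluate change". The baseline check dates the pre-intervention score at T1 for both groups. Nothing in the section dates the post-intervention score.

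Elsewhere the protocol article dates that score in three ways:

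- **By group.** Method has "post intervention (T2 for IIG and T3 for DIG". The list of measurable quantities in Programme evaluation agrees, describing the programme's immediate impact as assessed "using immediate pre and post-data from both groups – IIG [T1 and T2]; and DIG [T2 and T3".
- **By calendar, the same for everyone.** Programme evaluation also says that children in both groups receive "three self-report questionnaires at pre (T1), post (T2), and follow-up (T3 and T4) intervention".
- **T3 for both groups.** The fourth hypothesis in Between group effects refers to "results obtained on the RCADS at post-intervention (T3" and then to follow-up in both groups at T4. For the IIG, T3 is elsewhere the three-month follow-up.

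Three other statements bear on intent. Programme evaluation gives the DIG the wait-list control role over T1 to T2. The second between-group hypothesis expects lower anxiety in the IIG than in the DIG at T2. The third expects no difference between the IIG at T2 and the DIG at T3.

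**The concern.** A wait-list design identifies the programme's effect only while one group is treated and the other is still waiting. Here that is T1 to T2. The efficacy test must therefore end the DIG window at T2, whether the outcome is a change score or a score at one time point.

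The term that sets the end of the window is the one with conflicting meanings. An analyst who takes the definition in Method at face value would end the DIG window at T3, after that group has had the programme. Starting at the DIG's own pre-intervention point gives T2 to T3. Starting at the T1 label in Statistical analyses gives T1 to T3. Either way, treated children are compared with treated children over different calendar windows. An effective programme could then look ineffective, and a trend shared by all children could look like a group difference. If the window stays open, it could also be chosen after the data are seen, with very different answers available.

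**Working it through.** **No figure to reproduce.** The article gives no alpha, effect size, SD or power calculation, so the check compares the windows that its wording allows.

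**Inputs from the article.** 30 children per group (Method); Mann-Whitney test on change scores (Statistical analyses); IIG treated between T1 and T2, DIG between T2 and T3 (Programme evaluation); one-week test-retest correlations of 0.65 to 0.80 for the RCADS scales (Participant outcomes).

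**Assumptions, not from the article.** Two-sided 5% level; normal scores with SD 1; within-child correlation r between waves of 0.5, 0.65 or 0.8 (the waves are weeks apart, so a value below the one-week range is included); effect d of 0.3, 0.5 or 0.8 SD, maintained after treatment; no dropout.

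**Step 1: expected contrasts.** Let the programme lower scores by d in the IIG and d′ in the DIG. Let t1 and t2 be the shared time changes over T1–T2 and T2–T3. The IIG change from T1 to T2 is t1 − d. The expected difference, IIG minus DIG, is then:

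- A, T1–T2 in both groups: (t1 − d) − t1 = −d
- B, DIG T2–T3: (t1 − d) − (t2 − d′) = −(d − d′) + (t1 − t2)
- C, DIG T1–T3: (t1 − d) − (t1 + t2 − d′) = −(d − d′) − t2

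Only A returns the programme's effect, and shared drift cancels from it. With d = d′ and no drift, B and C are exactly zero.

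**Step 2: rejection rates.** Simulation, 20,000 replicates per setting, equal effects, no drift:

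| r | d | A | B | C |
|---|---|---|---|---|
| 0.5 | 0.3 | 0.191 | 0.048 | 0.050 |
| 0.5 | 0.5 | 0.456 | 0.049 | 0.048 |
| 0.5 | 0.8 | 0.840 | 0.049 | 0.047 |
| 0.65 | 0.3 | 0.257 | 0.048 | 0.048 |
| 0.65 | 0.5 | 0.593 | 0.051 | 0.048 |
| 0.65 | 0.8 | 0.942 | 0.043 | 0.044 |
| 0.8 | 0.3 | 0.413 | 0.048 | 0.049 |
| 0.8 | 0.5 | 0.832 | 0.050 | 0.048 |
| 0.8 | 0.8 | 0.997 | 0.048 | 0.047 |

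**Step 3: hand check of one cell in A.** The SD of change is √(2(1 − r)). At r = 0.65 this is √0.70 = 0.837. The standard error of the difference is 0.837 × √(2/30) = 0.216. At d = 0.5, 0.5/0.216 − 1.96 = 0.355, so power is Φ(0.355) = 0.64 for a comparison of means. With the Mann-Whitney efficiency of 0.955 under normality it is 0.62, close to the simulated 0.59.

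**Step 4: drift.** By the formulas in step 1, a shared fall of 0.2 SD over T1–T2 only (t1 = −0.2, t2 = 0) gives B an expected difference of −0.2 SD. A fall of 0.2 SD in each period gives C +0.2 SD, in the wrong direction. In 4,000 replicates at r = 0.70 and d = 0.5, each of these was declared significant 16% of the time. Contrast A rejected in 66% of replicates under either drift.

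**The case against.** The strongest reply is that the intended window can be recovered from the text. Statistical analyses labels the pre-intervention score T1 for both groups, which fits the calendar scheme (T1, then T2) and not a DIG window starting at T2. The second hypothesis sets the comparison of treated with waiting children at T2. The DIG is named as control over T1 to T2. The third hypothesis lists IIG T2 against DIG T3 separately and expects no difference, so the authors already see that comparison as a null one. The group-specific pairs given for immediate impact match the two within-group hypotheses, and nothing says the pairs are contrasted with each other. No listed comparison uses DIG change from T1 to T3.

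All of this stands. A reader might infer that the planned test does compare treated with treated children and cannot detect the programme's effect. The article does not support that, because Statistical analyses never mentions T3 and the rest of the text favours T1 to T2. Nor does the simulation show which window will be used: with equal effects, the null result in B and C follows by construction. The drift figures depend on an assumed trend.

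A further reply is that a full analysis plan would fix the window. That would answer a missing detail. Here the article states the contrast and gives its key term meanings that conflict.

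**Conclusion.** The point holds as an inconsistency in a term on which the only named between-group efficacy test depends. T2 minus T1 in both groups is the more plausible intent, but Statistical analyses does not say so, and the definition in Method points to T3 for the DIG.

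The choice of window matters a great deal. The T3 readings reject at about the type I error rate whatever the effect, which requires only equal effects in the two groups and no time trend. A difference found under those readings could reflect unequal effects, a time trend or chance. Power under T1 to T2 runs from 0.19 to 0.997 in the table and depends wholly on the assumed effect and correlation, so it is illustrative only. This is a should-fix correction of wording, and it is not proof that the planned test cannot work.

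**What to change.** 1. In Statistical analyses, state that the efficacy contrast compares T2 minus T1 between the IIG and the DIG, and that the DIG score at T2 is the end of its untreated wait, not a post-intervention score.
2. State that DIG change from T2 to T3 is reported only as that group's within-group result and does not enter the efficacy contrast.
3. Use one meaning of post-intervention in Method, Programme evaluation, Between group effects and Statistical analyses. The simplest is IIG T2 and DIG T3, with plain time labels (T1 to T4) wherever both groups are described together. The common schedule in Programme evaluation and the fourth hypothesis would then need relabelling.

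The cost is about one or two sentences and a few labels. No visits, children or data are added.

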## Discussion

This study will employ a randomised wait-list control group design with pre and post-intervention measures to evaluate the effectiveness of a specifically tailored, group-based, CBT anxiety intervention programme for 9–13 year old South African children with visual impairments. It is hypothesised that children in the IIG will experience significantly reduced symptoms of anxiety when compared to children in the DIG.

